### Criteria for discontinuing or modifying allocated intervention/comparator {15b}

At each weekly visit, participants will be asked if they have made a quit attempt in the past week.

If a participant has made a quit attempt in the past week, research staff will:Encourage the participant to continue abstaining from smoking.Schedule normal weekly visits.Provide the participant with the tobacco quitline number.Offer the option to either take home the study product or decline it. If the participant chooses to take home the study product, recommend they store the product out of sight to avoid smoking triggers.

If the participant declines the study product, instruct them to contact the research coordinator if they lapse and would like to pick up the product before the next visit.

For the safety concerns, participants will be withdrawn immediately from the study if any of the following occur:Cardiovascular disease (CVD) event: Typically includes MI (heart attack), PTCA (angioplasty/stenting), bypass surgery, stroke, peripheral vascular disease (arterial blockages in arms or legs leading to procedure or surgery). Less common CVD problems would be new cardiac arrhythmias (e.g., new atrial fibrillation) or new valvular disease (e.g., mitral or aortic regurgitation).DVT/PE (deep vein thrombosis/pulmonary embolism, i.e., blood clots in the venous system).Psychiatric Hospitalization: A subject will be withdrawn if they are hospitalized for psychiatric reasons at any time during participation in the study.Pregnancy: If subject indicates they are pregnant or have a positive pregnancy test after receipt of study products, they will be withdrawn from the study if they are continuing to use any tobacco product, and the pregnancy will be documented as an adverse event that will remain open until delivery. At that time the research staff will contact the participant to ask a few questions about the baby’s health and will update the open Adverse Event.Expired breath CO increase: A subject will be withdrawn from the study if the average of the 2 CO readings is 100 ppm or greater.

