### Secondary outcomes

The following outcomes will be based on 7 days’ daily logs submitted through text message prompted surveys during the last week of the trial (before the week 4 visit). Use of other combusted (e.g., little cigar and cigarillos) and noncombusted (e.g., e-cigarettes) products will be assessed by asking participants to enter an integer indicating the number of each product used per day. Use of nicotine replacement therapy (NRT) or prescription cessation medications will be assessed using a multiple-choice question, allowing participants to select all NRT or prescription cessation medications used from a provided list of options.

The following outcomes will be based on a questionnaire completed during the week 4 visit. Perceived risks of smoking VLNCs will be measured by asking participants’ perceived likelihood of overall harm to health under conditions of smoking VLNCs [33]. Response options range from 1 (Not at all likely) to 5 (Extremely likely), with higher scores representing a better outcome. An additional option, “Don’t know,” is also provided. Self-efficacy to quit smoking will be measured with multiple items, assessing perceptions about the strength of confidence in one’s ability to quit smoking [34]. Response options range from 1 (not at all) to 7 (extremely), with higher scores representing a better outcome. An additional option, “Don’t know,” is also provided. Nicotine dependence will be assessed using the Fagerstrom Test for Nicotine Dependence scale, a six-item questionnaire measuring the quantity of cigarette consumption, the compulsion to use, and dependence [35].

Forgoing cigarettes will be assessed using daily logs submitted throughout the 4 weeks of the trial, with two items asking whether participants chose to skip cigarettes they normally would have smoked and whether they stubbed/butted out a cigarete before finishing it [34, 36]. Response options are as follows: 1 (no), 2 (yes, once), and 3 (yes, several times), with higher scores representing a better outcome. Quit intention will be measured with multiple items asking participants’ intention and motivation to quit in the next month and 6 months [37]. Response options range from 1 (not at all) to 7 (extremely), with higher scores indicating a strong intention to quit. An additional option, “Don’t know,” is also provided.

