### Sample size {19}

In the randomized clinical trial, participants will be randomized into one of two conditions: treatment (VLNCs with messages) or control (VLNCs only). We will conduct three separate trials, each targeting a specific group of people who smoke: (1) individuals with serious psychological distress (SPD), (2) individuals with low SES (defined as having a high school education or less or with household income less than 200% of the federal poverty level), and (3) individuals who are neither of those two groups. For each group, we will have 262 participants to complete the 4-week study. This number accounts for a 20% attrition during the 1-week baseline and an additional 20% attrition during the study period; thus, we will enroll 410 participants and randomize 328 participants to achieve 262 completes for each smoker group. The projected attrition rates are conservative and are based on our own studies and past RCTs with VLNCs [39–41], including with the same priority populations (e.g., 24% attrition during an intensive 8-week study that used ecological momentary assessments in the similar populations in Atlanta, GA [42]; 18% attrition for a 12-week study with smokers with low SES and mental health conditions [13]).

Based on the above assumptions and adjusting for missing data (0–20%) in daily logs, with 262 participants in each participant group completing our study, we will be able to detect the following effect sizes. For data collected in daily logs (28 observations per person): primary outcome (cigarettes per day) and secondary outcomes (use of other tobacco products, cessation medications, and foregoing cigarettes), the study has sufficient (0.80) power to detect small effect sizes (*d* = 0.11–0.17, depending on the level of autocorrelations and missing data). For data collected in weekly in-person visits (5 observations per person): secondary outcomes related to cessation behaviors, perceptions, and physiological responses, the study has sufficient power to detect small-to-medium effect sizes (*d* = 0.27–0.38, depending on the level of autocorrelations and missing data). Cohen’s definition of effect sizes will be used (small *d* = 0.20, medium *d* = 0.50, large *d* = 0.80 [43, 44]).

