For binary outcomes, such as making a quit attempt, we will be able to detect odds ratios (OR) between 1.27 and 1.41 for daily log data (28 observations per person, depending on the level of autocorrelations and missing data) and OR = 1.74–2.22 for weekly data (5 observations per person). Past research found baseline values of 35% for the proportion of participants who tried to quit using VLNCs [41]. We will be able to detect small effect sizes (small OR = 1.68, medium OR = 3.47, large OR = 6.71 [45]).

Overall, the study is sufficiently powered to detect small effect sizes, which is necessary based on past research that found that messaging campaigns have at most small effects [46, 47].

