## Statistical methods

### Statistical methods for primary and secondary outcomes {27a}

We will conduct intent-to-treat analysis. All participants who were originally assigned to different treatment conditions are analyzed as part of their original conditions, regardless of whether they completed the treatment or adhered to the protocol. Analyses will be performed using SAS or R software. All statistical tests will be two-tailed (*α* = 0.05). The treatment condition will be compared to the control condition; if significant differences are observed (*p* < 0.05), the results will be interpreted as evidence of treatment effect.

Descriptive statistics for all measurements will be reported separately for each trial (people who smoke with SPD, with low SES, and with neither). Frequency distributions will summarize categorical data, and measures of central tendency and dispersion will summarize continuous data. All data will be examined for bivariate relationships with the outcomes and with each other.

For each trial, the primary analysis will be regression models to test the difference in the mean CPD (cigarettes smoked per day) between those in the treatment condition and those in the control condition, adjusting for the baseline CPD value and other covariates that are strongly correlated with the outcome (*r* ≥ 0.3) [49]. Analyses of secondary outcomes will be similar to the analysis of the primary outcome. We will use multivariable regression models to examine differences between the treatment and the control arm while accounting for potential covariables.

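### The unrestricted claim of power for small effects contradicts the plan's own figures for visit-based secondary outcomes, and its odds-ratio benchmarks do not fit the 35% rate quoted beside them

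*Protocol article*

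**What the plan says.** All figures are in the protocol article, Sample size {19}, unless another section is named.

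- **Daily-log outcomes, including the primary outcome:** "the study has sufficient (0.80) power to detect small effect sizes", with d = 0.11–0.17.
- **Weekly-visit outcomes:** detectable d = 0.27–0.38, which this section itself labels small-to-medium. The d cut-offs are 0.20 (small), 0.50 (medium) and 0.80 (large).
- **Binary outcomes, with making a quit attempt as the example:** OR 1.27–1.41 for daily-log data, and "OR = 1.74–2.22 for weekly data (5 observations per person".
- **Base rate:** "Past research found baseline values of 35% for the proportion of participants who tried to quit using VLNCs".
- **OR benchmarks, given directly after that rate:** "We will be able to detect small effect sizes (small OR = 1.68, medium OR = 3.47, large OR = 6.71".
- **Summary:** "Overall, the study is sufficiently powered to detect small effect sizes, which is necessary based on past research". The reason given is that messaging campaigns have, at most, small effects.

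Two other places bear on which range applies to which outcome. On quit attempts, the discontinuation criteria {15b} say: "At each weekly visit, participants will be asked if they have made a quit attempt in the past week"; Table 2 marks quit attempts at visits and leaves the daily-log column empty. For perceived risk, self-efficacy and dependence, the Secondary outcomes section says: "The following outcomes will be based on a questionnaire completed during the week 4 visit".

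**The concern.** The section makes power for small effects a requirement and then says without qualification that it is met. Its own figures meet that requirement for one class of outcome and miss it for the other. The outcomes that miss it include perceived risk, self-efficacy, quit intention and dependence, which carry most of the second and third aims.

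The OR benchmarks add to the difficulty. They are set beside a 35% rate but appear to belong to a much rarer event, so a detectable OR of 1.74 looks almost small when at 35% it is well above small. A reader who relies on the summary sentence would give a null result on a visit-based outcome more weight than the design supports.

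**Working it through.** **Inputs.** Two-sided α = 0.05 ("All statistical tests will be two-tailed (*α* = 0.05", section {27a}); power 0.80; 262 completers per group at 1:1, so 131 per arm; the detectable effects, cut-offs and 35% rate listed above. z(0.975) + z(0.80) = 1.960 + 0.842 = 2.802.

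**1. The plan's own figures.** The attrition chain reproduces: 410 × 0.8 = 328, and 328 × 0.8 = 262.4. The detectable d ranges cannot be reproduced uniquely, because the article gives no autocorrelation. With m equally correlated observations, d = 2.802 × √[(2/131)(1 + (m − 1)ρ)/m]. For m = 5 and an assumed ρ = 0.5 this is 0.268, in line with the stated lower end of 0.27. The ranges are therefore taken as stated below.

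**2. Detectable effects against the plan's own small cut-offs.**

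| Outcome type | Detectable | Plan's small | Within small? |
|---|---|---|---|
| Daily log, d | 0.11–0.17 | 0.20 | yes |
| Visit, d | 0.27–0.38 | 0.20 | no, whole range above |
| Daily log, OR | 1.27–1.41 | 1.68 | yes |
| Visit, OR | 1.74–2.22 | 1.68 | no, whole range above |

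**3. Power at a small effect, if 80% power holds at the stated values.** Power = Φ(2.802 × 0.20/d − 1.960).

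- d = 0.27: Φ(0.115) = 0.55.
- d = 0.38: Φ(−0.486) = 0.31.
- For comparison, the daily-log range gives above 0.99 (d = 0.11) and 0.91 (d = 0.17).

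The same formula on the log-OR scale gives power at OR 1.68 of 0.75 (detectable OR 1.74) and 0.45 (detectable OR 2.22).

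**4. Base rate implied by the OR benchmarks.** Convert d at base rate p0 by p1 = Φ(Φ⁻¹(p0) + d) and OR = [p1/(1 − p1)]/[p0/(1 − p0)]. Example at 35%: Φ⁻¹(0.35) = −0.385; adding 0.2 gives −0.185; p1 = 0.4265; OR = (0.4265/0.5735)/(0.35/0.65) = 1.38.

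| Base rate | d = 0.2 | d = 0.5 | d = 0.8 |
|---|---|---|---|
| Plan states | 1.68 | 3.47 | 6.71 |
| 0.5% | 1.76 | 3.85 | 7.84 |
| 1% | 1.685 | 3.474 | 6.708 |
| 2% | 1.61 | 3.13 | 5.75 |
| 35% | 1.38 | 2.23 | 3.62 |
| Logistic, exp(dπ/√3) | 1.44 | 2.48 | 4.27 |

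Only the 1% row matches all three stated values, up to rounding.

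**5. Weekly ORs on the d scale at 35%.** OR 1.74 takes 35% to 48.4%, so d = Φ⁻¹(0.484) − Φ⁻¹(0.35) = 0.34. OR 2.22 takes 35% to 54.4%, so d = 0.50. The logistic conversion, ln(OR) × √3/π, gives 0.31 and 0.44.

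**6. Outcomes defined at week 4 alone.** With one unadjusted comparison, d = 2.802 × √(2/131) = 0.346. This lies inside 0.27–0.38, but the lower end of 0.27 belongs to five observations. Baseline adjustment multiplies the value by √(1 − r²). At an assumed baseline-to-week-4 correlation of 0.5 or 0.6 it becomes 0.30 or 0.28.

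**The case against.** The strongest reply is that little is concealed. The visit-based range is already labelled small-to-medium, 0.27 is closer to 0.20 than to 0.50, and OR 1.74 is only about 4% above 1.68. That stands as a limit on severity, but it does not reconcile the text: the summary sentence drops the qualification, and neither visit-based range reaches its own small cut-off even at its favourable end.

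Some stronger readings go further than the document allows:

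- **That the whole trial, or its primary outcome, lacks power for small effects.** The stated daily-log d of 0.11–0.17 is below 0.20, and nothing in this point challenges it.
- **That visit-based outcomes are powered for moderate effects only.** The stated range begins at 0.27, so small-to-medium is the fair description.
- **That the daily-log ORs have no use.** The section speaks of binary outcomes generally, and use of cessation medication is asked in the daily log. Only the example is misplaced. Quit attempts also do not appear among the outcomes described under Secondary outcomes, although Table 2 lists them as an outcome.
- **That the stated visit-based ranges are wrong and should give way to d = 0.35, or to OR of about 2.0 for quit attempts.** Both values lie inside the stated ranges. They assume one unadjusted comparison, whereas section {27a} plans baseline adjustment for the primary outcome and similar analyses for the secondary ones, and no passage fixes quit attempts at a single visit.

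Two cautions on the benchmarks also stand. The 1% rate is inferred, since the article does not state it and the cited source was not available. The 35% comes from past research with no time window given, while this trial asks about the past week, so its fit to the weekly analysis is not established.

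**Conclusion.** The point holds for visit-based secondary outcomes. By the plan's own numbers their detectable effects exceed its small cut-offs throughout, and power at d = 0.20 is about 55% to 31%, provided that 80% power holds at the stated d values. The OR benchmarks do not match the 35% rate quoted with them. Under the normal-shift conversion, small at 35% is OR 1.38 (1.44 under the logistic conversion), and the weekly OR range corresponds to d of about 0.34–0.50 (0.31–0.44 logistic). Quit attempts come under the weekly range, because they are scheduled only at visits.

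Severity is moderate: a stated power property is wrong for one class of secondary outcome. The sample size, the primary-outcome statement and the analysis are not touched.

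**What to change.** In Sample size {19}:

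1. Limit the small-effect statements to daily-log outcomes, where the stated d figures support them. Say that visit-based secondary outcomes are powered for small-to-medium effects only.
2. Replace 1.68/3.47/6.71 with benchmarks for the 35% rate and name the conversion: about 1.38/2.23/3.62 (normal shift) or 1.44/2.48/4.27 (logistic). Under the first, the upper daily-log OR of 1.41 is marginally above small; under the second it is not.
3. Attach the daily-log ORs to a binary outcome collected in the daily log, such as cessation-medication use, and the weekly ORs to quit attempts.
4. For outcomes defined at week 4 alone, note that the five-observation lower end of 0.27 does not apply without baseline adjustment, and that one unadjusted comparison of 131 versus 131 needs d of about 0.35.

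The cost is rewording the power statements in one section. The stated power for visit-based outcomes becomes less favourable; recruitment and conduct do not change.

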### Recruitment {20}

The study has a comprehensive, multipronged recruitment strategy that focuses on media, community outreach, and strong partnerships with local healthcare systems and community partners, with targeted recruitment of racially/ethnically diverse smokers with SPD and low SES in Atlanta, GA.

At GSU, participants will be recruited through flyers (posted at venues including local community health centers, near MARTA and bus stops, community centers and shelters, etc.) and media (e.g., radio; print media in local newspapers and buses/trains). We will stimulate recruitment by giving presentations, talking with staff, providing study information, and supplying flyers at local clinics and community organizations. Participants will also be recruited through online sources (e.g., Craigslist) and by word of mouth. Individuals interested in participation will leave their contact information on a voicemail or on a form on our website. GSU research staff will call each participant and describe the study in detail. After obtaining verbal consent, the participants will be asked questions over the phone to determine initial eligibility. If eligible and interested, they will be scheduled for an in-person baseline visit.

In addition, at Grady and Emory, participants will be recruited through flyers placed in clinics and distributed by clinician partners, which will include a link to the screening questionnaire. The self-reported smoking status and other eligibility criteria of potential participants will be confirmed by a research coordinator via phone. Those who are eligible and interested will be scheduled for an in-person baseline visit.

#### Assignment of interventions: randomization

### Sequence generation: who will generate the sequence {21a}

During the randomization visit (after 1-week baseline), a separate computer-generated allocation sequence will be created for participants at each site using stratified randomization to ensure balance across conditions.

### Sequence generation: type of randomisation {21b}

Participates will be stratified by readiness to quit (planning to quit in the next 6 months vs. not) and menthol preference (menthol vs. non-menthol). Within each stratum, participants will be randomized in a 1:1 ratio to either the treatment (VLNCs + messages) or the control (VLNCs only) condition.

### Allocation concealment mechanism {22}

To ensure allocation concealment, randomization results will be stored in REDCap, accessible only to the research team members responsible for allocation.

### Implementation {23}

A research coordinator at each site will work with the PI, Co-I, and clinical staff at Grady to enroll participants and assign participants to the trial conditions.

## Assignment of interventions: blinding

### Who will be blinded {24a}

Trial participants will be blinded to the study hypotheses. They will be informed that they will be randomized to view (or not) campaign messages related to VLNCs.

### How will be blinding be achieved {24b}

Blinding is limited to concealing the study hypotheses from participants. Consent materials state only that participants may or may not view VLNC-related messages, without specifying hypotheses about expected effects.

### Procedure for unblinding if needed {24c}

N/a. There are no planned circumstances under which unblinding would be required, as the nature of the message intervention does not pose risks necessitating disclosure of group assignment.

## Data collection and management

### Plans for assessment and collection of outcomes {25a}

Data will be obtained via participant self-report surveys during in-person visits (collected using the REDCap system) and through daily logs (using the Twilio text messaging integration with REDCap), in addition to biochemical testing (expired CO for biochemical verification of smoking status) during in-person visits.

Standard operating procedures will be applied to each visit and procedure to ensure consistency. PI and Co-Is will train research staff and ensure quality control throughout the study, where the protocol and procedures will be carefully described. Case Report Form books will be created to maximize parallel recording of data across studies. Each visit will have a checklist of all the measures that need to be administered and the order in which these measures are administered. Additionally, online meetings will be held regularly with the lead site PIs and coordinators.

### Plans to promote participant retention and complete follow-up {25b}

Participants will receive financial compensation for the time and inconvenience associated with participation: $50 for each in-person visit, $10 per visit to defray the cost of travel; and $5 for each completed daily log, as past research shows that compensating for each assessment (and reminding participants of that) increases retention [48]. Participants will receive cash compensation at each weekly visit. If participants withdraw from the study or do not complete certain parts, they will be compensated for the portions they complete. If they are unable to attend the final in-person visit, they have the option to receive a gift card in the mail. The maximum compensation is $535/person.

### Data management {26}

Questionnaire data will be collected and managed using the REDCap (Research Electronic Data Capture) system available at Georgia State University. This will provide a secure way to collect and manage data while avoiding potential issues with manual data entry. Georgia State University and Emory (Co-I [name]) belong to a consortium of institutional partners that work to maintain a software toolset and workflow methodology for electronic collection and management of research data. REDCap data collection projects rely on a study-specific data dictionary defined by the research team. The research team can create and design surveys in a web browser and engage potential respondents using a variety of notification methods. Both REDCap and REDCap Survey systems provide secure, web-based applications that are flexible enough to be used for a variety of types of research, provide an intuitive interface for users to enter data, and have real-time validation rules (with automated data type and range checks) at the time of entry. These systems offer easy data manipulation with audit trails and reporting for monitoring, reporting, and querying patient records, and an automated export mechanism to common statistical packages (SPSS, SAS, Stata, R/S-Plus). The REDCap application is securely housed in Amazon AWS and managed by the Research Solutions department at Georgia State University. All web-based information transmission is encrypted, and the data are encrypted at rest. Amazon AWS’s data centers are state-of-the-art, nondescript, and secure facilities. Data will be downloaded from REDCap into a secure server that is managed by Georgia State University or Emory, password-protected, and available only to research personnel who have completed training in research with human subjects.

